#### Criteria for discontinuing or modifying allocated interventions {11b}

Participants will be allowed to withdraw their consent to participate in the cohort or the intervention at any time without personal disadvantages or having to give a reason. If a participant withdraws from the cohort or intervention, no additional data will be collected, but any data collected up to that point will be included in the analysis as permitted by General Data Protection Regulation (GDPR) when using public task as the legal basis (GDPR Art. 6(1)e, 9(2)j) [26]. Information about voluntary participation and the possibility to withdraw at any time will be emphasised in the participant information leaflet, while information on data processing will be provided in the privacy notice. There will be no special criteria for discontinuing or modifying allocated interventions; other than required adjustments in case of COVID-19 restrictions; placement provision will adhere to any adaptive working arrangements as may be required, while contact between participant; and case manager and/or within work familiarisation sessions will in this case be completed by phone and video.

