### Trial design {8}

We will use a single-site cohort randomised approach. The trial will be conducted within a superiority framework. Initially, all eligible and consenting participants will be recruited for an observational cohort study. After baseline measurement, we will randomly select one in three, to whom we will offer the intervention and request consent for intervention participation. Figure 1 illustrates the plan for the delivery of the intervention using a cascade diagram [14]. Assessments will be made at baseline and at 3-, 6-, and 12-month follow-up, and the primary outcome of return to work will be obtained from questionnaire and registry data at these time points. We will also use registry data at all follow-up time points to estimate hospital and community health and social care use for our economic analysis from a personal social services perspective. A pre-pilot informs logistical processes and pre-pilot participants may be included in the main trial if there are no substantial protocol amendments during the pre-pilot, or as a result of piloting (i.e. no alteration in the cohort and intervention delivery). Parallel to the intervention, we will run a process evaluation exploring implementation, continuity of the provided package, reasons for participating and declining participation, and mechanisms behind cases of sustained return to work. The study will be reported following the CONSORT guideline (Consolidated Standards of Reporting Trials; http://www.consort-statement.org/) extension for the reporting of randomised controlled trials conducted using cohorts and routinely collected data (Fig. 2) [15]. The study protocol has been written using the structured protocol template for Standard Protocol Items: Recommendations for Interventional Trials (SPIRIT) Checklist for intervention trials [16].

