### Outcomes {12}

### Primary outcome measure

#### Sustained return to work

There is no consensus in the literature about what constitutes a sustained return to work. In trials of return-to-work interventions, outcome measures have been expressed with employment success constituting as little as one day of paid work [28]. However, we consider the focus on sustained return to work more useful and relevant [29]. Thus, in this study, the primary outcome will be the proportion of participants achieving a sustained return to work, which we define as the first 4 weeks of 50 to 100% work. We will examine the differences between the cohort group and intervention group, with differences at 12 months being the primary end-point. For a sustained return to work, the primary outcome data will be collected using Norwegian Labour and Welfare Administration registry data, and self-report data at 3, 6, and 12 months from baseline measurement in the case of missing registry data.

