### Participant timeline {13}

A participant timeline was created according to the SPIRIT guidance and is presented in Fig. 3 [58]. Following admission to the cohort study, baseline measurement will be completed. After baseline measurement, one in three will be randomly selected to be invited to the intervention (see SPIRIT item 16a). If wishing to join the intervention, the participant will be assigned a case manager who will conduct the initial assessment. The case manager will then match the participant to a suitable work placement in collaboration with Manpower. The participant, case manager, and placement supervisor will agree and sign a return to work plan, and the participant will attend a 2-day work familiarisation session prior to the 6-week placement. Self-reported follow-up questionnaires will be completed by all participants 3, 6, and 12 months after baseline.

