### Statistical methods

#### Statistical methods for primary and secondary outcomes {20a}

A detailed statistical analysis plan has been finalised and agreed prior to analysis by the research team. We will report all participant flow in line with the CONSORT guideline extension for reporting RCTs conducted using cohorts and routinely collected data showing withdrawal and loss to follow-up [15]. Analyses will be conducted within TSD using Stata v17 or above (Stata Corporation, College Station, TX). Participant characteristics and outcomes will be summarised as mean and standard deviation for normally distributed continuous data or with median and ranges for data with skewed distributions or counts and percentage for categorical data. The primary analysis approach will be ‘intention-to-treat’. To account for the trial design featuring clustering in the intervention arm, generalised linear (GLM) mixed effects models will be used to estimate the between-group differences for both primary and secondary continuous outcomes, adjusting for age, gender, and duration of pain, with a random intercept for case manager. For example, we will analyse the between-group differences in sustained return to work (a binary outcome) using a generalised mixed-effect model with logit link function, the above covariates, and fitting a random effect in case manager allocation.

Secondary outcomes will also be analysed using generalised mixed models, using link functions appropriate to the outcome (e.g. where outcomes are continuous, we will use a canonical link function). In all cases, we will adjust for the same covariates (i.e. age, gender, and duration of pain). The adjusted treatment effect estimates (mean difference) between the groups will be presented as point estimates within a 95% confidence interval. Our outcome measures are largely independent and no correction for multiple testing will be done. *P*-values < 0.05 will be considered statistically significant. All tests will be two-sided.

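### As written, withdrawing from the intervention alone ends all follow-up, so the offered arm can lose 12-month outcomes by a route the controls do not have

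*Protocol article*

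**What the plan says.** Item 11b names two separate acts: "Participants will be allowed to withdraw their consent to participate in the cohort or the intervention at any time". It then gives one data rule for both: "If a participant withdraws from the cohort or intervention, no additional data will be collected". Earlier data are kept: "any data collected up to that point will be included in the analysis".

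Only the selected participants are asked for the second consent. Under Trial design (item 8), "we will randomly select one in three, to whom we will offer the intervention and request consent for intervention participation".

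Other sections assume complete follow-up:
- Participant timeline (item 13): "Self-reported follow-up questionnaires will be completed by all participants 3, 6, and 12 months after baseline".
- Cost-effectiveness (under Outcomes): self-report and registry data are planned for every study participant.
- Primary outcome: taken from the welfare-administration (NAV) registry, with self-report as back-up, "with differences at 12 months being the primary end-point".
- Statistical methods (item 20a): "The primary analysis approach will be ‘intention-to-treat".
- Additional analyses (item 20b): a CACE analysis, with adherence defined by placement weeks attended (two for minimal, six for full).
- Missing data (item 20c): missingness will be assessed, and imputation is a conditional sensitivity analysis.

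**The concern.** The rule ties outcome collection to staying in the intervention, although the outcome does not depend on it. Registry status and a postal or online questionnaire can be obtained from someone who has left a placement, and the cohort consent is separate from the intervention consent.

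Only the offered arm has an intervention to withdraw from, so the rule opens a route to missing outcomes in that arm alone. Those lost are likely to differ from those who stay, because leaving the intervention is itself a form of non-adherence. At stake are the primary comparison at 12 months, the CACE analysis, which needs outcomes from non-adherers, and some power.

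**Working it through.** **1. Does any section restore follow-up?** Item 11b separates the two withdrawals and then joins them under one rule. No other section limits that rule to intervention-process data or says that cohort follow-up continues after withdrawal from the intervention alone. Items 13 and 20a and the Cost-effectiveness text presuppose follow-up that the rule would end.

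**2. When would withdrawal fall?** The Discussion reports a mean of 94.8 days from baseline to the start of placement in the feasibility study. Adding a 6-week placement gives 94.8 + 42 = 136.8 days, about 4.5 months. With similar timing, withdrawal before or during placement comes well before 12 months.

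**3. The plan's own sample size (item 14).** Inputs: 30% v 10%, two-sided 5%, 80% power, three controls per intervention participant. The two-proportion formula with continuity correction gives 44 + 132 = 176, as stated. Inflation gives 44 × 1.14 / 0.80 = 62.7, rounded up to 63, and 132 / 0.80 = 165; 63 + 165 = 228, as stated. The 20% loss is the same in both arms, with no allowance for extra loss in one.

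**4. Bias in the intervention rate.** Let *p* be the arm's true rate, *w* the share lost through intervention-only withdrawal (beyond the planned 20%, with no sustained return recorded beforehand), and *r* the return rate among those lost. Then

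observed rate = (*p* − *w* × *r*) / (1 − *w*).

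The protocol gives neither *w* nor *r*; the values below are assumptions. Biases in percentage points are in brackets.

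| *w* | *p* = 10% (no effect), *r* = 0 | *p* = 30%, *r* = 0 | *p* = 30%, *r* = 10% |
|---|---|---|---|
| 10% | 0.10/0.90 = 11.1% (+1.1) | 0.30/0.90 = 33.3% (+3.3) | 0.29/0.90 = 32.2% (+2.2) |
| 20% | 0.10/0.80 = 12.5% (+2.5) | 0.30/0.80 = 37.5% (+7.5) | 0.28/0.80 = 35.0% (+5.0) |
| 30% | 0.10/0.70 = 14.3% (+4.3) | 0.30/0.70 = 42.9% (+12.9) | 0.27/0.70 = 38.6% (+8.6) |

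If *r* = *p* the bias is zero. If *r* exceeds *p* it is negative: with *p* = 10% and *r* = 20%, it is −1.1 points at *w* = 10% (0.08/0.90 = 8.9%) and −4.3 at *w* = 30% (0.04/0.70 = 5.7%).

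**5. Power.** With *n*₁ intervention and *n*₂ = 132 control participants,

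power = Φ[(0.20 − ½(1/*n*₁ + 1/*n*₂) − 1.96 × SE₀) / SE₁],

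where SE₀ is the pooled and SE₁ the unpooled standard error. At *n*₁ = 44: SE₀ = 0.0622, SE₁ = 0.0739, correction 0.0152, so Φ(0.853) = 80%. For *w* = 10%, 20% and 30%, *n*₁ is 39.6, 35.2 and 30.8, and power is 77%, 74% and 70%. This holds the true rates at 30% and 10% and counts only the loss of numbers.

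**The case against.** **The sentence can be read distributively.** Leaving the cohort would end cohort data, and leaving the intervention would end only case-manager forms, diaries and interviews. That fits the two consents and the sections that promise follow-up of everyone. The reading is possible, but the protocol does not state it, and staff following the text literally would stop everything. The point is therefore about what the text instructs, not proof that follow-up has stopped.

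**The rule reaches fewer people than a reader might infer.** One might conclude that everyone who quits is lost and that those who stay are compared with all controls. The text does not support this. The trigger is withdrawal of consent: people who decline the offer, or stop attending without withdrawing consent, remain in follow-up, and controls can also lose data by leaving the cohort. For the same reason CACE loses some of its non-adherers, not all.

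**Earlier data are kept.** A sustained return already recorded still counts. This limits the loss, and limits any reversed bias to people who withdraw before their return is recorded. It does not help those whose status is still open at withdrawal.

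**Intention-to-treat survives in form.** A reader might infer that the rule rules it out. It does not: participants can still be analysed as allocated, and item 20c provides for examining missingness. The comparison is weakened by missing outcomes. How missing data are modelled may properly sit in the analysis plan, which is not shown, but no analysis plan recovers outcomes that were never collected.

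**Conclusion.** The point holds as a defect of wording with a real consequence if followed. Item 11b ends follow-up for offered participants who formally withdraw from the intervention alone, including the 12-month primary end-point unless a sustained return is already on record. That conflicts with item 13 and the Cost-effectiveness text, weakens the intention-to-treat comparison in item 20a, and takes some non-adherers from the CACE analysis in item 20b.

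The size is conditional. At an assumed 10–30% loss with no returns among those lost, the bias is about +1 to +4 points with no true effect and +3 to +13 points under the design rates; the upper figures are worst cases. Direction and size depend on how often the lost participants return to work, which the protocol cannot tell us. No stated figure is wrong: 176 and 228 both reproduce.

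**What to change.** Split the rule in item 11b:
- Withdrawal from the intervention alone ends intervention contact and the collection of intervention-process data. Questionnaires and registry follow-up continue under the cohort consent.
- Withdrawal from the cohort stops all new data collection, with earlier data kept as now.

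Bring the participant information leaflets and privacy notice into line, and check item 11b against the Cost-effectiveness text and items 13, 20a and 20b. The sample size stays at 176 analysable and 228 recruited.

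The cost is more than an edit. Item 25 routes amendments to the ethics committee and the data-protection body where approval is required. Trial status gives a recruitment start of January 2023, with pre-pilot recruitment from September 2022, so participants already enrolled would have to be told of the change. If the distributive reading was intended, the amendment only states it, but the leaflets must still say the same.

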#### Strategies to improve adherence to interventions {11c}

##### Participant adherence

To increase adherence to data collection and decrease the risk of dropout, participants will be given reminders, and their response rates will be monitored by the trial manager. The trial manager will be responsible for reminding participants of data collection appointments and being available to answer questions and concerns. Participants in the intervention group will be matched with a case manager who provides support throughout the 6-week placement and will answer any questions the participant may have about the intervention.

##### Implementation and staff adherence

Case managers will use a standardised form developed for reporting contact with participants, and templates for their initial assessment and return to work plan ensuring that case managers adhere to the same procedures. The case manager and facilitator training component, resource package, and standardised templates are informed from experience from the UK feasibility study and modified for Norwegian consumption [13]. The training will be recorded so each staff member can revisit the training component as needed. Additionally, members of the trial working group will participate in the training, thus being able to provide a stand-in service if necessary. Other strategies to improve adherence include trial manager liaison with case managers, staffing provider, and placement manager.

### Adherence monitoring

Monthly meetings with the Trial Management Group will include a review of monitoring and oversight, deviations, violations, breaches, and risk assessment. Spirit items 5d and 21a describe the composition and role of the Trial Steering Committee (TSC) and Data Monitoring Committee (DMC), which both are important for adherence monitoring. The process evaluation will include monitoring of the numbers and reasons for participant drop-out and procedures used to facilitate continued participation, fidelity to the conceptual model and the extent to which the familiarisation sessions and intervention were implemented as designed; reasons for health referrals, and intervention acceptability and adherence [27].

### Relevant concomitant care permitted or prohibited during the trial {11d}

Participants in both the cohort group and the intervention group will be free to seek other forms of care or use any medication during the trial. Within the intervention, the case manager will support any participant who needs to consult for work-related healthcare, which will be registered as part of secondary outcomes in the study.

### Provisions for post-trial care {30}

The intervention aims to tackle obstacles to work and create an individual plan to return to work. Some participants may be referred to work-related healthcare by their general practitioner during the intervention. In cases of prolonged need for healthcare, the individuals will maintain a dialogue with their general practitioner, this being independent of the intervention.

### Outcomes {12}

### Primary outcome measure

#### Sustained return to work

There is no consensus in the literature about what constitutes a sustained return to work. In trials of return-to-work interventions, outcome measures have been expressed with employment success constituting as little as one day of paid work [28]. However, we consider the focus on sustained return to work more useful and relevant [29]. Thus, in this study, the primary outcome will be the proportion of participants achieving a sustained return to work, which we define as the first 4 weeks of 50 to 100% work. We will examine the differences between the cohort group and intervention group, with differences at 12 months being the primary end-point. For a sustained return to work, the primary outcome data will be collected using Norwegian Labour and Welfare Administration registry data, and self-report data at 3, 6, and 12 months from baseline measurement in the case of missing registry data.

### Secondary outcome measures

Secondary outcome measures will be health-related quality of life, work ability, pain and pain intensity, and satisfaction with care, and we will examine the between-group differences at 3, 6, and 12 months after baseline measurement. These outcomes are selected to reflect important domains associated with work, unemployment, and return to work [30–33]. The EQ-5D-5L will be used to measure the potential changes in participants’ self-reported health-related quality of life within five domains: mobility, self-care, usual activities, pain/discomfort, and anxiety/depression. The WEMWBS measures mental well-being [34], while the PROMIS-29 will be used as the outcome for related domains: anxiety, depression, fatigue, pain (intensity and interference), physical function, sleep disturbance, and social participation [35]. Work-related outcomes include numeric scale measures in confidence in return to work and work ability a return to work self-evaluation and offers of employment. For those who have returned to work, measures include usual work patterns, job satisfaction, and the WRQF, an outcome measure linking a person’s health to the ability to meet work demands [36].

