We will collect follow-up data at 3, 6, and 12 months from baseline measurement, where we additionally will ask about return to work, job offers, or usual care and services, and then, for those who have returned to work: satisfaction with work, the Work Role Functioning Questionnaire (WRFQ) [51, 52], and return to work self-efficacy [53–55] whether work makes the pain worse, healthcare and social care use, medication, and the amount of time they have been at work (Table 1). The WRQF has been cross-culturally adapted into Norwegian using guidelines proposed by Beaton et al. [56, 57]. Johansen et al. examined the internal consistency reporting Cronbach’s alpha coefficients for sub-scales were well-zoned, ranging between 0.80 and 0.90 [57]. The return-to-work self-efficacy scale has been translated into Norwegian and been assessed using principal components analysis, in addition to studies of internal consistency and concurrent validity. Cronbach’s alpha was high enough to indicate the potential for redundant items, although PCA outlined a three-factor structure matching the original instrument. The authors conclude that the instrument has satisfactory cross-cultural validity [55].

In general, there is an absence of work
examining reliability and responsiveness of these instruments, which we will
acknowledge as a limitation.

**Table 1 Tab1:** Outcome domains, measurement instruments, and measurement time points

Domain	Measurement instrument or key items within the questionnaire package	Abbreviation	T0	T1	T2	T3
Demographic	N/A		X			
Pain	Troublesome grid		X			
	Pain duration		X			
Work-related baseline	Educational level		X			
	Unemployed duration		X			
	Looking for work duration		X			
	Reasons for wanting to RTW		X			
Health-related quality of life	Health-related quality of life	EQ-5D-5L	X	X	X	X
	Warwick-Edinburgh Mental Well-being Scale	WEMWBS	X	X	X	X
	Patient Reported Outcome Measurement Information System 29	PROMIS 29	X	X	X	X
	Pain intensity		X	X	X	X
Details of care received and services used	Registry data: Norwegian patient register, Municipal patient and user register, and Control and payment of health reimbursements		X	X	X	X
	Received any care or help for pain last three months* or since the last questionnaire		X*	X	X	X
	List of used medications in last three months* or since the last questionnaire		X*	X	X	X
Work-related	Dimensions of Work Ability		X	X	X	X
	Confidence in RTW		X	X	X	X
	RTW self-evaluation		X	X	X	X
	Job offers			X	X	X

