	Return to work			X	X	X
For those who return to work	Satisfaction with work			X	X	X
	Pain interference with work			X	X	X
	Work pattern			X	X	X
	Work-role functioning	WRFQ		X	X	X
Sustained RTW (Primary)	Registry data from the Norwegian Labor and Welfare Administration			X	X	X
Adverse events	Case Report Forms			X	X	X

*Last three months for baseline measurement

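### Work measures collected only from people back at work are not exempted from the between-arm models, so the text as written leads to a comparison that randomisation does not protect

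*Protocol article*

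**What the plan says.** Under Secondary outcome measures the protocol introduces a group of work measures with a restriction: "For those who have returned to work, measures include usual work patterns, job satisfaction, and the WRQF". The same sentence describes that questionnaire as an outcome measure. The paragraph on follow-up data (under Cost-effectiveness) repeats the restriction: "for those who have returned to work: satisfaction with work, the Work Role Functioning Questionnaire (WRFQ". Table 1 places satisfaction with work, pain interference with work, work pattern and the WRFQ under the row label "For those who return to work", at the three follow-up visits and not at baseline.

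The sentence that announces arm comparisons has its own list of subjects: "Secondary outcome measures will be health-related quality of life, work ability, pain and pain intensity, and satisfaction with care". It continues: "we will examine the between-group differences at 3, 6, and 12 months after baseline measurement". The returner-only measures are not in that list.

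Statistical methods for primary and secondary outcomes {20a} then states a general rule: "Secondary outcomes will also be analysed using generalised mixed models, using link functions appropriate to the outcome". On covariates it says "In all cases, we will adjust for the same covariates (i.e. age, gender, and duration of pain", and on reporting "The adjusted treatment effect estimates (mean difference) between the groups will be presented as point estimates within a 95% confidence interval". The Framework section applies superiority testing to the outcomes in general. Nothing in the article exempts the returner-only measures, calls them descriptive, or says how selection into work is to be handled.

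**The concern.** Randomisation makes the two arms comparable as whole groups. It does not make those who return to work in one arm comparable with those who return in the other, because the intervention is meant to change who returns. If it succeeds, its returners will include people who would not have returned under usual care. A difference in work-role functioning or job satisfaction among returners then mixes any effect on the score with a difference in who is being scored.

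Age, gender and pain duration would remove this only if they captured everything that drives both return to work and the score, which is implausible. The measures have no baseline value, so adjustment on the same scale is not available either. At stake is a mean difference with a confidence interval and P value that readers take for a treatment effect, when it could arise with no effect on anyone's score.

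**Working it through.** **Inputs.** From Sample size {14}: return to work 10% in the cohort group, a difference of 20 percentage points (so 30% in the intervention group), 80% power, 5% significance, 132 control and 44 intervention participants, 20% loss, design effect 1.14. Two-sided testing is from {20a}.

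**1. Reproduce the plan's own figure.** Two proportions, three controls per intervention participant, mean proportion (0.30 + 3 × 0.10)/4 = 0.15:

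- Uncorrected intervention n = [1.960 × √((4/3) × 0.15 × 0.85) + 0.842 × √(0.30 × 0.70 + 0.10 × 0.90/3)]² / 0.20² = 37.2, rounded up to 38.
- With continuity correction: 44 intervention and 132 control, total 176, as stated.
- Inflation: (132 + 44 × 1.14)/(1 − 0.20) = 227.7, i.e. 228, as stated.

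The planning rates are therefore understood correctly. They refer to sustained return to work.

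**2. How many would contribute.** The protocol gives no rate for any return to work. If it were near the sustained-return rates: control 132 × 0.10 = 13.2; intervention 44 × 0.30 = 13.2. That is about 13 v 13, drawn from one tenth of one arm and three tenths of the other. Any return is the broader state, so actual numbers could be larger.

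**3. How different the two sets could be.** If the intervention only adds returners and removes none (assumption), the share of intervention returners with no counterpart among control returners is (0.30 − 0.10)/0.30 = 67%.

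**4. Size of the bias under one illustrative model.** Assume a standard normal employability score U. In each arm the top fraction p returns to work. The measured score correlates ρ with U, and treatment has no effect on it. Then E[U | top p] = φ(c)/p, with c = Φ⁻¹(1 − p):

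- p = 0.10: 1.755
- p = 0.30: 1.159
- Difference, intervention minus control: 1.159 − 1.755 = −0.596

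The spurious difference is ρ × (−0.596), in SDs of the score in the whole population:

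| Return rates (control v intervention) | ρ = 0.1 | ρ = 0.3 | ρ = 0.5 | ρ = 0.7 |
|---|---|---|---|---|
| 10% v 30% (planning rates) | −0.06 | −0.18 | −0.30 | −0.42 |
| 10% v 20% (assumed) | −0.04 | −0.11 | −0.18 | −0.25 |
| 20% v 40% (assumed) | −0.04 | −0.13 | −0.22 | −0.30 |
| 5% v 25% (assumed) | −0.08 | −0.24 | −0.40 | −0.55 |

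The values of ρ are assumptions; the protocol gives none. The negative sign comes from the model, in which added returners are less employable and so score lower. If added returners scored higher than those who return anyway, the sign would reverse.

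**5. Precision.** At 13.2 v 13.2, the smallest difference detectable with 80% power is (1.960 + 0.842) × √(2/13.2) = 1.09 SD.

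**The case against.** The strongest reply is that the protocol never says these measures will be compared between arms. A reader might infer an explicit promise from the between-group clause, but its stated subjects are quality of life, work ability, pain and satisfaction with care. The returner-only measures come later, introduced simply as measures. The general statement in {20a} could be read as covering only the listed outcomes, no secondary objective asks for the comparison, and a finalised SAP exists that may treat these measures separately.

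Much of this stands. The comparison is inferred, not stated. It is still the natural reading: the measures sit under the secondary outcome heading, one is called an outcome measure, and {20a} and Framework give a rule without exception. The listed subjects are broad domains and also omit confidence in return to work and job offers, so absence from that list does not settle the matter. For pain interference with work the inference is weaker, since its restriction appears as a row in Table 1 and not in the secondary outcome text. The concern is the unqualified rule in the protocol, not detail left to an unseen SAP.

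Three stronger readings are not supported:

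- A reader might infer that the contrast conditions on the primary outcome itself. The primary outcome is four weeks at 50 to 100% work, taken from registry data; the restriction here is any return to work, and Table 1 lists the two separately.
- A reader might infer that an effective intervention will look harmful. Placements are matched to skills and aspirations, and accommodations are discussed, so added returners could score better or worse.
- A reader might infer that a falsely significant result is likely. At about 13 v 13 the detectable difference of 1.09 SD is well above the illustrative biases, so an imprecise and uninterpretable estimate is more likely.

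**Conclusion.** The point holds in this form: four measures exist only in a subset formed after randomisation by something the intervention aims to change, and the protocol's general rule sends secondary outcomes to an arm comparison without excluding them. Followed literally, the rule gives a contrast that randomisation does not protect and that the three covariates cannot be relied on to repair.

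The size is not known. The figure of −0.06 to −0.42 SD rests on the threshold model, the planning rates and assumed correlations of 0.1 to 0.7. The count of about 13 v 13 borrows sustained-return rates for a broader state. The loss of comparability needs only that the intervention changes who returns, which is the trial's own hypothesis. The primary analysis, the sample size and the secondary outcomes measured in everyone are not affected.

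**What to change.** Add a sentence to Statistical methods {20a}, with a matching qualification in Framework, that WRFQ, job satisfaction, work pattern and pain interference with work are excluded from the between-group models. They should be reported by arm descriptively, with the number contributing, labelled as non-randomised, and with no effect estimate or P value. Align the SAP if it does not already say this.

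Any formal comparison should use an estimand defined over all randomised participants. Ranking those not working lowest is one option, but at the planning rates it would tie about 90% of controls and 70% of intervention participants at the bottom. It would then largely repeat the return-to-work comparison and say little about functioning at work, so it is optional.

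The cost is a change of wording and the loss of P values for these measures. No change to data collection, sample size or primary analysis follows.
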